**Fig. 1 Fig1:**
[figure not shown]
Study flowchart

### Online intervention platform

The technology platform used to deliver the ICare Prevent intervention is provided by Minddistrict. This company is full partner of the ICare project consortium and responsible for the provision and maintenance of the platform. Its content management system is used to upload the interventions, add new participants and eCoaches, as well as questionnaires. Access to the platform is provided by means of email and personalized password combination. It is currently used both in clinical research and in routine practice to provide guided and unguided self-help interventions for a variety of mental health conditions. The platform conforms to all required quality standards and operates according to the ISO 27000 and NEN 7510 norms. All data are securely stored on ISO 27000 certified servers and transmitted using HTTPS with SSL certificates (AES-256 and SHA-1, 2048-bit RSA). Unauthorized access to the platform is therefore not possible. A data management and safety plan has been developed as part of the larger ICare project.

### Intervention

ICare Prevent is an Internet-based intervention with mobile-support by means of an application (app). It uses both transdiagnostic and individually tailored components that are based on previously developed Internet-based modules, all using evidence-based CBT principles [47–51]. ICare Prevent consists of seven main sessions and one booster session. Participants are advised to complete one main session per week. The intervention contains text, exercises, images, explanatory videos, as well as audio files and downloadable information. Testimonials are used to illustrate (homework) exercises. The main sessions follow the same basic structure. First, the content of the current session is explained, followed by a review of the homework exercises from the previous session. In accordance with the individually tailored approach of the intervention, participants can choose content depending on their predominant complaints, i.e. depression or anxiety. For example, in the fifth session, participants can either practice problem-solving or exposure techniques. The content per session is summarized in Table 1. Throughout sessions 2–7, participants can choose to complete one of eight choice modules following the main intervention content. In accordance with the transdiagnostic approach of the intervention, these modules aim at increasing resilience and tackle problems common to both depression and anxiety. In addition, five diaries with different content, such as positive activities and sleep, are accessible through the online platform and the app. An overview of all choice modules and diaries is given in Table 2.

**Table 1 Tab1:** Overview of topics covered by the intervention per session

Session	Topic
1	Introduction, technical aspects, goal-setting, and behavioral activation in the context of basic psychological needs and important personal values
2	Identifying problems and tackling them through behavioral activation
3	Psychoeducation on depression and anxiety
4	Cognitive restructuring and challenging negative thoughts
5	Identifying the most prominent complaints and accordingly follow either:
	a) problem-solving strategies for more prominent depressive complaintsb) exposure strategies for more prominent anxiety complaints
6	Deepening the training on the route chosen in session 5
7	Making a plan for the future
8	Booster session (four weeks after session 7)

**Table 2 Tab2:** Overview of topics covered by the choice modules and diaries

Choice module	Topic
1	Sleep
2	Perfectionism
3	Gratitude
4	Self-esteem
5	Alcohol consumption (includes AUDIT-C)
6	Relaxation
7	Acceptance
8	Rumination
Diary	Topic
1	Positive activities
2	Negative thoughts
3	Sleep
4	Challenging situations
5	Alcohol consumption

The intervention can be used on (laptop) computers, mobile phones, and tablets. The mobile app can be used optionally. It provides access to the diaries and allows participants to activate push notifications. These short messages contain small exercises, such as short relaxation techniques, as well as motivational texts. The intervention uses a responsive web design in order to tailor content to participants’ needs, based on the choices they make. An optional read-aloud function is included. The expected time to complete each session is approximately 60 min. The two intervention conditions only differ in the support participants receive. In the guided condition, trained eCoaches (clinical psychology master students) spend approximately 20 min, but no more than 30 min per session on sending individual manualized feedback on the exercises through the intervention platform. In addition, they will send reminders for module completion in order to increase adherence. The eCoaches will be supervised by the members of the research team. Participants in the unguided condition receive only automatic motivational messages that aim to increase adherence by positively reinforcing participants for completing intervention modules and reminding them in case of a delay in completion.

### Care as usual (CAU)

Participants in all three conditions may use CAU services. We monitor healthcare services used, as well as other means to alleviate symptoms (e.g. as talking with relatives and friends), by means of a self-report questionnaire, the Client Service Receipt Inventory (CSRI; [52]). In the Netherlands, CAU for subclinical symptoms of depression and/or anxiety can include visits to the general practitioner, making use of support staff trained in the provision of help for mild psychological symptoms, or (student) psychologists according to Dutch guidelines [53, 54]. Alternatives include homeopaths, alternative medicine providers, or self-medication. Participants in the control group will receive access to ICare Prevent one year after trial inclusion.

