### Participants

Students will be recruited and provided with contact details through e.g. a website (https://icare-online.eu/nl/), social media (e.g. Facebook), and information material distributed on campus at Dutch universities. They are eligible if they: (1) are aged ≥ 16 years; (2) experience at least mild self-reported symptoms of depression, defined as a score ≥ 16 on the Center for Epidemiological Studies Depression scale (CES-D; [41]), and/or anxiety, defined as a score ≥ 5 on the seven-item version of the Generalized Anxiety Disorder scale (GAD-7; [42]); (3) do not meet diagnostic criteria for a mood or anxiety disorder based on the Mini International Neuropsychiatric Interview (M.I.N.I.; [43]) at screening. Exclusion criteria are: (1) being on a waitlist for, currently receiving, or having received psychotherapy over the past six months for any mental health condition; (2) meeting diagnostic criteria for a lifetime bipolar disorder (M.I.N.I.) or having received a diagnosis of a psychiatric disorder; (3) being at moderate to severe risk for suicide (M.I.N.I.); (4) being in remission of a major depressive disorder (MDD) episode, defined as an MDD diagnosis in the previous six months and experiencing at least one cardinal symptom (e.g. persistent and pervasive low mood, loss of interest or pleasure in usual activities) during the previous three weeks (M.I.N.I.); (5) self-reported inability to read or write Dutch; (6) no informed consent; (7) no access to a computer or the Internet; or (8) participating in similar studies at time of inclusion.

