### Study procedures

Upon contact, potential participants will receive an information letter and informed consent form by email, the latter to be signed and returned. In addition, the email contains a link to the ICare Prevent platform on which participants have to register. After the informed consent form has been returned, the screening questionnaires for all self-reported inclusion and exclusion criteria will be made available on the platform. The screening consists of: demographic questions; the CES-D; and the GAD-7. Next, eligible participants will be asked for their telephone number in order to conduct the M.I.N.I. interview, the clinician rated version of the Quick Inventory for Depression Scale (QIDS-CR; [44]) and the Structured Interview Guide for the Hamilton Anxiety Rating Scale (SIGH-A; [45]). The interviews will be performed by trained clinical psychology master students under the supervision of a member of the research team; 10% will be recorded and rated by a second rater to assess inter-rater reliability. Consent for the recordings will be asked for at the beginning of the call. Disagreement between raters will be solved by discussion or by asking an experienced psychotherapist. Eligible participants will receive a confirmation by email and access to the baseline self-report questionnaires on the online platform. Once completed, they will be randomized to one of the two intervention conditions or the control group.

Non-eligible participants will be advised to consult their general practitioner or a (student) psychologist if they think they need help for their complaints. Those with moderate to severe suicide risk will also be advised to contact their general practitioner. In addition, they will be informed about the national suicide helpline (113online; [46]). The research team will contact those participants again one week later and ask whether they sought help.

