### Measures

Following screening and baseline (all groups), assessment points for the intervention groups include five weeks after randomization or directly after session 5 (whichever happens first) and eight weeks after randomization or post intervention (whichever happens first). Assessment points for the control group include five and eight weeks after randomization. Follow-up measures for all three groups consist of six and 12 months after randomization. Assessments include self-report questionnaires on the intervention platform and diagnostic interviews administered over the telephone. An overview of all measures taken by assessment point is given in Table 3.

**Table 3 Tab3:** Overview of instruments with associated assessment points

Measure (instrument)	Assessment point					
	T0	T1	T2	T3	T4	T5
Screening						
Depression (CES-D)	X					
Anxiety (GAD-7)	X		X	X	X	X
Demographic data	X					
Mental disorder diagnosis self-reported	X					
Experience with psychotherapy	X					
Clinical diagnosis (M.I.N.I.)	X				X	X
Primary outcomes						
Depression (QIDS)	X			X	X	X
Anxiety (SIGH-A)	X			X	X	X
Secondary outcomes						
Depression (PHQ-9)		X	X	X	X	X
Anxiety (GAD-7)	X		X	X	X	X
Clinical diagnosis (M.I.N.I.)	X				X	X
Academic performance (PSS, ECTS)		X	X	X	X	X
Cost-effectiveness						
Costs (CSRI)		X			X	X
Other outcomes						
Alcohol use (AUDIT-C)		X	X	X	X	X
Alliance (WAI-SR)^a^			X			
Behavioral activation (BADS-SF)		X		X	X	X
Reasons for dropout^a^				X		
Expectations (CEQ)		X				
Incongruence (INKK)		X		X	X	X
Motivation (TEQ)		X	X	X		
Negative effects of treatment (INEP)^a^				X		
Personality (BFI-10)		X				
Potential risk factors^b^		X				
Program evaluation (CSQ-8)^a^			X	X		
Quality of life (AQoL, EQ-5D-8 L)		X		X	X	X
Resilience (CD-RISC)		X	X	X	X	X
Sleep quality (PSQI)		X		X	X	X
Support^a^			X			
Wellbeing (WHO-5)		X		X	X	X
Worry (PSWQ-3)		X		X	X	X

^a^Only in intervention groups

^b^Optional

*T0* screening, *T1* baseline, *T2* after completion of session 5 or 5 weeks after randomization, *T3* post intervention, *T4* 6-month follow-up, *T5* 12-month follow-up

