### Secondary outcomes

Secondary outcomes include self-reported reduction in depressive and anxiety symptoms from baseline to post intervention. In addition to screening, the GAD-7 will be used to measure anxiety symptoms throughout the trial. The nine-item Patient Health Questionnaire (PHQ-9; [62]) will be used to assess depressive symptoms. Research on the PHQ-9 has generally shown good psychometric properties among all age groups [62–64]. Moreover, the time to onset of a mood or anxiety disorder within the 12-month follow-up period will be assessed by the M.I.N.I. Finally, academic performance will be measured by the Presenteeism Scale for Students (PSS; [65]). It is a valid and reliable measure that will be used to assess presenteeism in the student population [65]. In addition, students will be asked to provide the number of points they acquired on the European Credit Transfer System (ECTS) during the semester.

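### Control access to ICare Prevent opens on, or possibly before, the day the 12-month assessment (T5) falls due, and nothing makes it wait for T5 to be completed

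*Protocol article*

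**What the plan says.** The section Care as usual (CAU) sets the control arm's access by date: "Participants in the control group will receive access to ICare Prevent one year after trial inclusion". The section Measures sets the last two assessments by a different starting event: "Follow-up measures for all three groups consist of six and 12 months after randomization".

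Study procedures gives the order of events before randomization. After the screening interview, "Eligible participants will receive a confirmation by email and access to the baseline self-report questionnaires on the online platform". Then: "Once completed, they will be randomized to one of the two intervention conditions or the control group".

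The article does not define inclusion. The word appears in the last exclusion criterion under Participants, "participating in similar studies at time of inclusion", which belongs to the eligibility stage. The Abstract, however, speaks of 252 students being included, and the sample size section splits the same 252 into 84 per arm, which points to the randomized sample.

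On how T5 is collected, Measures says: "Assessments include self-report questionnaires on the intervention platform and diagnostic interviews administered over the telephone". No window for T5 is printed.

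**The concern.** A waiting control arm stays a clean comparator only until it is given the intervention. Here the release date and the last assessment are both set at one year, but from differently named starting events, and release does not depend on the assessment having been done. Some control data labelled as 12-month usual care could therefore come from people who already have the programme.

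T5 matters for several outcomes. Table 3 schedules the M.I.N.I. after screening only at six and 12 months, and the cost questionnaire after baseline only at six and 12 months. Each thus has two follow-up observations, and T5 is one of them. The M.I.N.I. feeds a named secondary outcome: "the time to onset of a mood or anxiety disorder within the 12-month follow-up period will be assessed by the M.I.N.I". Disorder-free days and QALYs are the effect measures of the economic evaluation. The clinician-rated and self-reported symptom scales are also repeated at T5.

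**Working it through.** The protocol gives no figure to reproduce here. The check compares dates.

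**Definitions**
- L = days from inclusion to randomization. L is zero or more if inclusion is at or before randomization (order of events in Study procedures).
- R = days from the T5 due date to actual completion of T5. R is taken as zero or more.

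**Dates**
- Access opens at: randomization + 12 months − L.
- T5 falls due at: randomization + 12 months.
- T5 is completed at: randomization + 12 months + R.

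**Results**
- Access date minus T5 due date = −L. This is never positive, so access never opens after T5 falls due.
- Possible access before T5 data are taken = L + R.

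**The two readings of inclusion**
- Inclusion = randomization: L = 0. Access opens on the due day, and possible exposure is R. A control who completes T5 on the due day, before access opens, has none.
- Inclusion = confirmed eligibility: L is the time taken to complete the baseline questionnaires and be randomized. Possible exposure is L + R, so even a punctual control can have had access for L days.

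**Illustration.** The document gives neither L nor R. The values below are assumptions. Sessions are counted at the advised pace ("Participants are advised to complete one main session per week"), with seven main sessions in all.

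| L (days) | R (days) | L + R (days) | Main sessions possible | L as share of 365 days |
|---|---|---|---|---|
| 0 | 0 | 0 | 0 | 0% |
| 0 | 14 | 14 | 2 | 0% |
| 7 | 7 | 14 | 2 | 1.9% |
| 14 | 14 | 28 | 4 | 3.8% |
| 28 | 28 | 56 | 7 | 7.7% |

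The last column matters for measures that accumulate over the year. Access before the 12-month point covers L/365 of the period, at most 28/365 = 7.7% in this range. A score of current symptoms at T5 is more exposed, because it reflects the participant's state after all L + R days.

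**What lies outside the problem.** The primary outcome runs from baseline to post intervention, about eight weeks after randomization. The self-reported depression and anxiety outcomes are defined over the same interval. These, the mid-intervention assessment and the six-month follow-up are all taken long before access opens.

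**Effect of the fix.** If access follows completion of T5, possible exposure before T5 data is zero for every L and R.

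**The case against.** The strongest reply has three parts.

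First, inclusion probably means randomization, since the 252 included are the 252 allocated. The two clocks then start together and only late T5 responders are exposed. This is a fair reading and it stands: the article does not establish that access opens before T5 is due. It does not remove the problem, because access on the due day still precedes every late T5.

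Second, this is a condensed article. The flowchart and the SPIRIT material are not shown, and the full protocol or the platform procedures may release access only after T5. The article also does not say that release is automatic, so shared use of the platform for questionnaires and programme does not prove that a control could start the programme first. That caution is right about operational detail. But the article is not silent on the point. It states a date rule, and the rule followed as written permits access before T5 is completed.

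Third, little is at stake. The primary outcome is untouched, the limitations section already calls the trial too small for time to onset (with pooling across the ICare trials planned), and the accumulating measures are touched only at the end of the year. This stands and limits the weight of the point.

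**Conclusion.** The point holds as a risk to control-arm T5 data. It does not show that contamination will occur. It rests on inclusion being at or before randomization and on some controls completing T5 after access has opened. The data at risk are control-arm symptom and quality-of-life scores taken at T5 and, for the last days or weeks only, time to onset, disorder-free days, QALYs and costs. If the programme works, the likely direction is toward no difference.

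Three stronger readings are tempting and are not supported.

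- **A percentage loss of the 12-month effect.** Dilution could be written as the share of controls using the programme times the fraction of its effect reached by T5. With 30% use and half the effect it is 0.30 × 0.5 = 15%; with 10% to 50% use it is 5% to 25%. If only 30% of controls are late and 30% of those use it, it is 0.30 × 0.30 × 0.5 = 4.5%. All these inputs are assumed and none is in the document, so no size can be derived. The formula also fits only scores taken at one point in time, not measures accumulated over the year.
- **Unblinding of T5 raters.** The randomization section already has participants told not to reveal their allocation. A control who has just started the programme might confuse a rater, but nothing shows that blinding would fail.
- **Loss of an incentive to complete T5.** This is conjecture; the article gives no evidence on it.

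**What to change.** In Care as usual (CAU), replace the date rule with one tied to T5 and count from randomization. For example: *Control participants receive access to ICare Prevent once they have completed the T5 questionnaires and interview, or when the T5 window closes, whichever comes first; T5 is due 12 months after randomization.* Record each control's access date, so that any T5 data obtained after access can be identified.

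The cost is one sentence in the protocol, a matching edit to the information letter and a release setting on the platform. Some controls would wait slightly longer for access. Closure of the window still guarantees access for those who do not respond.

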### Measures

Following screening and baseline (all groups), assessment points for the intervention groups include five weeks after randomization or directly after session 5 (whichever happens first) and eight weeks after randomization or post intervention (whichever happens first). Assessment points for the control group include five and eight weeks after randomization. Follow-up measures for all three groups consist of six and 12 months after randomization. Assessments include self-report questionnaires on the intervention platform and diagnostic interviews administered over the telephone. An overview of all measures taken by assessment point is given in Table 3.

**Table 3 Tab3:** Overview of instruments with associated assessment points

Measure (instrument)	Assessment point					
	T0	T1	T2	T3	T4	T5
Screening						
Depression (CES-D)	X					
Anxiety (GAD-7)	X		X	X	X	X
Demographic data	X					
Mental disorder diagnosis self-reported	X					
Experience with psychotherapy	X					
Clinical diagnosis (M.I.N.I.)	X				X	X
Primary outcomes						
Depression (QIDS)	X			X	X	X
Anxiety (SIGH-A)	X			X	X	X
Secondary outcomes						
Depression (PHQ-9)		X	X	X	X	X
Anxiety (GAD-7)	X		X	X	X	X
Clinical diagnosis (M.I.N.I.)	X				X	X
Academic performance (PSS, ECTS)		X	X	X	X	X
Cost-effectiveness						
Costs (CSRI)		X			X	X
Other outcomes						
Alcohol use (AUDIT-C)		X	X	X	X	X
Alliance (WAI-SR)^a^			X			
Behavioral activation (BADS-SF)		X		X	X	X
Reasons for dropout^a^				X		
Expectations (CEQ)		X				
Incongruence (INKK)		X		X	X	X
Motivation (TEQ)		X	X	X		
Negative effects of treatment (INEP)^a^				X		
Personality (BFI-10)		X				
Potential risk factors^b^		X				
Program evaluation (CSQ-8)^a^			X	X		
Quality of life (AQoL, EQ-5D-8 L)		X		X	X	X
Resilience (CD-RISC)		X	X	X	X	X
Sleep quality (PSQI)		X		X	X	X
Support^a^			X			
Wellbeing (WHO-5)		X		X	X	X
Worry (PSWQ-3)		X		X	X	X

^a^Only in intervention groups

^b^Optional

*T0* screening, *T1* baseline, *T2* after completion of session 5 or 5 weeks after randomization, *T3* post intervention, *T4* 6-month follow-up, *T5* 12-month follow-up

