### Randomization, treatment allocation, and blinding

The allocation scheme will be derived by computer using a random number generator at a 1:1:1 ratio. Participants will be randomized at an individual level by an independent institute (University of Münster, Germany) and randomization will be stratified by type of subclinical symptoms (depression or anxiety). Due to the nature of the study it is not possible to blind either participants or coaches, as they will be notified to which of the three conditions they have been assigned to. However, raters who perform the clinical interviews to assess outcomes will be blinded. In order to ensure that blinding was successful, participants will be informed about the importance not to indicate their allocation status at the beginning of the telephone interviews. Moreover, raters will be asked to guess the allocation status of each participant after the second interview at post intervention. The results will then be compared to what would have been expected by chance. The flowchart of the trial is shown in Fig. 1.

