### Primary outcome

The primary outcome is change in disorder-specific symptom severity from baseline to post intervention. For depression, this will be assessed using the QIDS-CR [44]. This interview has been used in different settings and has good psychometric properties [44, 61]. The SIGH-A [45] will be used for the assessment of anxiety. Its reliability and validity has been found to be good [45].

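### The primary (T3) assessment has a completion-triggered clock in the active arms and a fixed week-8 clock in CAU, so measurement time depends on arm and adherence

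*Protocol article*

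**What the plan says.** All references are to the protocol article.

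- **Measures** gives two rules for one assessment. Intervention arms: "eight weeks after randomization or post intervention (whichever happens first"). Control arm: "Assessment points for the control group include five and eight weeks after randomization". The mid-intervention assessment (T2) follows the same pattern: in the active arms it takes place at week 5 or on finishing session 5, if that is sooner. The 6- and 12-month follow-ups run from randomization in all three arms.
- **Primary outcome**: "The primary outcome is change in disorder-specific symptom severity from baseline to post intervention". Table 3 places both interview instruments, the QIDS and the SIGH-A, at T3.
- **Intervention**: "ICare Prevent consists of seven main sessions and one booster session", and "Participants are advised to complete one main session per week". Table 1 adds "Booster session (four weeks after session 7").
- **Randomization, treatment allocation, and blinding**: "raters who perform the clinical interviews to assess outcomes will be blinded". The stated safeguard is that "participants will be informed about the importance not to indicate their allocation status at the beginning of the telephone interviews". Raters also guess the allocation after the post-intervention interview, and their guesses are compared with chance.

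**The concern.** The primary outcome is a change over time, so the arms should be measured after the same elapsed time. Here the active arms can only be measured at the same time as CAU or earlier, and who is measured earlier depends on how fast each person works through the programme. That pace is a post-randomization behaviour, so randomization does not balance it. It may also differ between the guided and unguided arms, because only the guided arm receives eCoach feedback and eCoach reminders.

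Two things are at stake. First, the contrast with CAU absorbs some difference in elapsed time. Entering actual time in the model would not fully remove this, because early measurement is itself a result of arm and adherence. Second, the date of a T3 call can carry information about allocation, and asking participants not to mention their arm does nothing about that.

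**Working it through.** **Design figure.** The plan's 252 (84 per arm × 3) can be reproduced: a group-by-time repeated-measures ANOVA with 3 groups, 2 time points, f = d/2 = 0.125, an assumed correlation of 0.5, α = 0.05 and power 0.95 gives N = 252. It plays no part in the timing argument; d = 0.25 serves below only as a yardstick.

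**Timing.** Inputs: 7 main sessions, an advised pace of 1 per week, and a week-8 cap in the active arms. Taking session 7 as the end, T3 in the active arms = min(8, 7 / pace), and T3 in CAU = 8.

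| Sessions per week | Session 7 at week | T3, active | Gap to CAU (weeks) |
|---|---|---|---|
| 0.8 | 8.75 | 8 (cap) | 0 |
| 1 (advised) | 7 | 7 | 1 |
| 1.5 | 4.7 | 4.7 | 3.3 |
| 2 | 3.5 | 3.5 | 4.5 |

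If *post intervention* instead means after the booster, the advised pace gives 7 + 4 = week 11, so week 8 comes first and the gap is 0. A gap would then arise only if session 7 were finished before week 4, that is, at more than 7/4 = 1.75 sessions per week. The parallel T2 rule, triggered by session 5, favours the session-7 reading, but the article does not settle it.

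At T2 the advised pace puts session 5 at week 5, so the gap there is 0 unless a participant goes faster. T2 carries self-report outcomes (PHQ-9, GAD-7), not the primary interviews.

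**Size of the shift.** Shift = drift per week × mean weeks early over *all* active participants, where mean weeks early = share finishing early × weeks early. The documents give none of these quantities, so all are assumptions.

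- Illustration: 0.4 SD over 8 weeks is 0.4 / 8 = 0.05 SD per week. With half finishing one week early: 0.05 × 0.5 × 1 = 0.025 SD, and 0.025 / 0.25 = 10%.
- Slower drift, low end: 0.02 × 0.25 × 1 = 0.005 SD, or 2%.
- Slower drift, high end: 0.04 × 0.75 × 3 = 0.09 SD, or 36%.

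If symptoms ease on their own, active participants measured early have had less time to improve, so this component understates the benefit.

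**Information carried by the date.** With 1:1:1 allocation, 168 are active and 84 are CAU. No CAU participant is due before week 8, so P(active | T3 before week 8) = 1. For a share p of active participants finishing early, P(CAU | T3 at week 8) = (1/3) / [(1/3) + (2/3)(1 − p)].

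| p (assumed) | Active participants assessed early | P(CAU given week 8) |
|---|---|---|
| 0 | 0 | 0.33 |
| 0.25 | 42 | 0.40 |
| 0.50 | 84 | 0.50 |
| 0.75 | 126 | 0.67 |

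These probabilities matter only to a rater who knows the time since randomization or what triggered the call.

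**The case against.** **Unblinding.** A reader might infer that blinding is lost at every early interview. The documents do not support that. Randomization is done by an independent institute and follows the screening interview, a confirmation email and the baseline questionnaires, so the interval from first interview to randomization varies. A call date alone therefore does not show weeks since randomization. The article does not say whether raters know the randomization date or the trigger; it neither establishes nor excludes it. Even a rater who knew would learn only active versus CAU, not guided versus unguided. The planned rater guess could detect a leak, though not prevent it. The objection stands as far as making the blinding point conditional.

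**Size.** A reader might also infer a shift close to the whole planned effect. For example, 0.6 SD of drift over 8 weeks and three weeks early gives 0.6 / 8 × 3 = 0.225 SD, or 90% of 0.25. That requires every active participant to finish three weeks early under a large drift that has no source in the documents. The advised pace gives one week, the cap gives slow users no gap, and the article itself names adherence as a worry, particularly without guidance. This objection stands.

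**Direction.** For a superiority trial, a shift from natural improvement is conservative. That is correct for this component. It does not settle the net direction, because measurement immediately after the last session, or the expectations of a rater who has become aware of allocation, could favour the active arms. The documents quantify neither.

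**Mitigation.** Later follow-ups share one clock and repeat both instruments, and time is a predictor in the model; whether that is actual or nominal time may be left to an analysis plan not shown. This helps the follow-up comparisons but not the primary time point.

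**Conclusion.** The timing asymmetry is written into the protocol and affects the primary endpoint: T3 falls at the earlier of completion and week 8 in the active arms, and at week 8 in CAU. On the session-7 reading, adherent participants are measured about a week or more before any control. On the booster reading the gap largely disappears, so the undefined term itself needs settling.

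The size of the bias cannot be derived from the documents. Under the illustrative assumptions it is about 0.025 SD (10% of d = 0.25), and other plausible inputs move it from 2% to 36%. The net direction is not established: it should be read neither as inflating the intervention effect nor as safely conservative. Disclosure of active allocation to raters is possible, not shown.

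**What to change.** - Schedule the T3 interview and questionnaires at a fixed time from randomization, with the same window in all three arms. Do the same for the outcome measures at T2. The later follow-ups already use this clock.
- Leave only process questionnaires (alliance, satisfaction, support) tied to session completion.
- Define *post intervention*, stating whether it refers to session 7 or the booster.
- State that raters are kept unaware of the randomization date and of what triggers a call.
- For participants already assessed under the present rule, add a sensitivity analysis using actual days since randomization. It describes the problem but does not fully correct it, because early timing depends on arm and adherence.

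The cost is a short amendment and a changed platform trigger; N = 252 is unaffected. Fast completers would wait a short time between their last session and T3. Recruitment began in July 2017, so some participants will have been assessed under the present rule and the primary endpoint will mix two schedules. The change should be coordinated with the sister ICare Prevent trials, which share similar procedures and whose data are to be pooled.
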